### **Statistical analysis in case control study**

Burton et al. [56] showed that 93 (48%) of patients with MUS diagnosed by secondary care physicians on two or more occasions and referred at least three times in the last five years had depressive and anxiety disorder compared to 38 (25%) patients only referred once to secondary care in the previous five years (odds ratio 2.6 (95% confidence intervals 1.6, 4.1). If these groups are assumed to be similar to the regular attenders and normal attenders in the current study, a sample size of 100 regular attenders and 100 normal attenders will have 90% power to show a difference at the 5 per cent level of significance on two tailed testing.

The regular attender and normal attender groups will be compared on the proportion with mental disorder (depressive disorder, anxiety disorder, somatoform disorder, overall prevalence of mental disorder), mean number of active physical health problems, distribution of severity of health anxiety, proportion of obesity on BMI, mean scores on smoking, alcohol consumption and exercise, and utility related quality of life on the EQ5D. Univariate analysis to test differences between the two groups will be performed using *t*-test for group means or geometric means if logarithm transformation is required for variables with skewed distribution. Chi-squared test will be used for group differences in categorical variables. The accuracy of recall by patients over the previous three months will be compared to health care contacts recorded in the primary care record. There is some evidence that regular attenders may not accurately recall health care contacts and do not realise how frequently they are attending compared to practice records [21,51].

Multivariate regression analyses conditional on case–control matched pairs will be conducted to identify factors significantly associated with frequency of primary care contacts by regular and normal attenders separately. Important variables (either statistically significant or clinically important) for each group of patients will be used in a discriminant analysis which could further select a list of variables that best reflect different characteristics of the two groups and separate them in principle of a maximum distance. In regression analysis we will use generalised linear model (GLM) so that different dependent variables will be analysed in different type of model, i.e. linear regression for continuous variables, logistic for binary and multinomial for categorical variables.

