#### **Recruitment**

Regular attenders will be identified from each practice and matched by age, gender and practice to a normal attender to control for practice and socio-demographic characteristics, by practice staff who will write to the patients to request their participation in the study. Approximately 100 regular attenders and 100 normal attenders will be recruited. Pilot work shows that 30-40% of regular attenders will agree to be interviewed but a higher proportion of normal attenders will agree to be interviewed. The representativeness of the selected regular attenders will be compared to the overall sample of regular attenders in the practices and the overall patient lists in terms of age and gender among those aged 18 years or over.

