In addition, information on active physical health problems currently and in the last two years, body mass index, smoking and alcohol consumption, and exercise will be extracted from practice records. The health care records will be examined 12 months later to ascertain health care use in the 12 month period following baseline assessment. Secondary health care use will be ascertained by exploring health care records over the preceding 10 years and prospectively over the next 12 months in all local secondary care services and nationally from Hospital Episode Statistics collected by the Department of Health for England.

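### Body mass index is extracted as a measurement but listed for group comparison only as the proportion obese, which under plausible assumptions gives away power; a minor point with a cheap fix

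*Protocol article*

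**What the plan says.** Under Procedures and measures, the protocol article states that "body mass index, smoking and alcohol consumption, and exercise will be extracted from practice records". BMI is therefore collected as a measurement.

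Under Statistical analysis in case control study, the list of group comparisons includes BMI only as the "proportion of obesity on BMI". Smoking, alcohol and exercise, in the same sentence, are compared as mean scores. Two kinds of univariate test follow. One is a t-test on means, or on geometric means where skewness calls for a log transformation. For the rest, "Chi-squared test will be used for group differences in categorical variables". Obese yes/no falls under the chi-squared test. No comparison of mean BMI is listed, and no reason is given for using the cut.

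The sample size rests on depressive and anxiety disorder, not BMI: "a sample size of 100 regular attenders and 100 normal attenders will have 90% power" to detect 48% against 25%, "at the 5 per cent level of significance on two tailed testing".

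**The concern.** Cutting a continuous measure at one point treats everyone on the same side of the cut as equal and usually weakens a comparison of groups. The BMI values are already in hand and the plan already has a suitable test, including one for skewed data, so the loss buys nothing that could not also be had by reporting both summaries.

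What is at stake is one line of secondary objective 2, the clinical characterisation of regular against normal attenders. The sample was sized for a large contrast in mental disorder. If BMI differs by a more moderate amount, the comparison of proportions has less chance of showing it than a comparison of means would.

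**Working it through.** **Inputs from the protocol article.** 100 per group (the Recruitment section says "Approximately 100 regular attenders and 100 normal attenders will be recruited"); two-sided 5%; planning rates for mental disorder of 48% and 25%.

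**Inputs that are assumed.** The article gives no obesity prevalence, BMI SD, cut-off or expected BMI difference. I assume normal BMI with equal SDs in the two groups, a shift of d SDs, and a control obesity prevalence p0. I take p0 = 25% as the central case and vary it from 15% to 50%.

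**1. The plan's own power figure.** For two proportions, with p̄ the average of p1 and p0 and n = 100:

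power = Φ[(|p1 − p0| − 1.96·√(2p̄(1 − p̄)/n)) / √(p1(1 − p1)/n + p0(1 − p0)/n)]

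With 0.48 and 0.25, p̄ = 0.365 and the two standard errors are 0.0681 and 0.0661. Then (0.23 − 1.96 × 0.0681)/0.0661 = 1.46, so power is 92.8%. Subtracting a continuity correction of 1/100 from the difference gives 90.5%. The matching sample sizes for 90% power are 90 and 99 per group. The stated 90% with 100 per group is reproduced with the correction.

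**2. BMI as a proportion and as a mean.** A shift of d SDs gives an obese share in regular attenders of p1 = 1 − Φ(z − d), where z is the normal quantile at 1 − p0. The power for the proportion is the formula above. The power for the mean is Φ(d/√(2/100) − 1.96).

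Example, d = 0.4 and p0 = 25%:
- Proportion: p1 = 1 − Φ(0.674 − 0.4) = 0.392 and p̄ = 0.321; (0.142 − 1.96 × 0.0660)/0.0653 = 0.19; power 57.6%.
- Mean: 0.4/0.1414 − 1.96 = 0.87; power 80.7%.

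| Shift (SD) | Obese share, regular attenders | Power, proportion | Power, mean | Loss (points) |
|---|---|---|---|---|
| 0.2 | 31.8% | 18.3% | 29.3% | 10.9 |
| 0.3 | 35.4% | 35.9% | 56.4% | 20.5 |
| 0.4 | 39.2% | 57.6% | 80.7% | 23.2 |
| 0.5 | 43.1% | 77.4% | 94.2% | 16.9 |
| 0.8 | 55.0% | 99.4% | 100.0% | 0.6 |

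Exact t-test power at 0.3, 0.4 and 0.5 SD is 56.0%, 80.4% and 94.0%, so the normal approximation makes no material difference.

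**3. Other control prevalences, d from 0.3 to 0.5.**

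| Controls obese | Loss (points) |
|---|---|
| 15% | 24 to 31 |
| 20% | 20 to 26 |
| 25% | 17 to 23 |
| 30% | 15 to 21 |
| 40% | 14 to 20 |
| 50% | 15 to 20 |

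Over all these prevalences the loss is 9 to 14 points at 0.2 SD and under 2 points at 0.8 SD.

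**4. Skewed BMI.** A simulation with log-normal BMI (assumed mean 27.5, SD 5.5, cut at 30, about 29% of controls obese) compared a t-test on log BMI with the chi-squared test. The losses were about 18, 20 and 14 points at 0.3, 0.4 and 0.5 SD on the log scale.

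**5. Unequal spread.** Keep p0 = 25% and let regular attenders' SD be r times the controls'. Then p1 = 1 − Φ((0.674 − d)/r), and the SD for the mean comparison is √((1 + r²)/2).

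| r | Shift (control SDs) | Power, proportion | Power, mean |
|---|---|---|---|
| 1.2 | 0.3 | 49% | 48% |
| 1.3 | 0.3 | 55% | 45% |
| 1.2 | 0.5 | 82% | 89% |

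At the 0.3 shift the advantage of the mean disappears at r = 1.2 and reverses at r = 1.3. At 0.5 with r = 1.2 the mean still leads.

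**The case against.** The strongest reply is that little depends on this. BMI and obesity are in none of the four hypotheses, BMI does not drive the sample size, and obesity is a recognised clinical category that suits an objective of clinical characterisation. Summary formats differ elsewhere in the same list too: mental disorder is compared as proportions and health anxiety as a distribution of severity. All of this stands. It limits the weight of the point, not its correctness.

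The second reply is that the loss depends on the model. That also stands: if regular attenders are more dispersed and differ mainly in the upper tail, the proportion obese may be the more sensitive comparison. This is a reason to keep the proportion, not a reason to leave the mean out.

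Third, 100 per group is approximate, BMI taken from practice records may be missing for some patients, and the calculation ignores the matching. The exact figures are therefore uncertain. Fewer values would lower the power of both comparisons.

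A reader might go further and infer three things that the article does not support:
- **That a loss of 17 to 23 points is a property of this plan.** It is not. It needs the assumed 25% control obesity, equal SDs and a shift of 0.3 to 0.5 SD.
- **That a moderate true difference will probably be missed.** Under the central assumptions the proportion has 58% power at 0.4 SD and 77% at 0.5 SD, so detection is more likely than not. Only at 0.3 SD (36%) is a miss the likelier result.
- **That BMI is used only as a binary variable throughout.** This holds for the listed univariate comparisons. The regression and discriminant analysis do not say in what form BMI would enter, and a condensed article may leave that to a fuller plan.

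**Conclusion.** The point holds as a minor one. The plan collects BMI, has a suitable test for its mean, and lists only the proportion obese, without giving a reason. With 100 per group, two-sided 5% and an equal-SD normal shift of 0.3 to 0.5 SD, this costs about 17 to 23 points of power at 25% control obesity and about 14 to 31 points across 15% to 50%. The cost is negligible for large differences, and it is not assured for small ones if the groups differ in spread. No hypothesis and no sample-size claim is affected.

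**What to change.** In Statistical analysis in case control study, add mean BMI to the measures compared by the t-test already planned, on the log scale if skewed, and keep the proportion obese alongside it. This changes one phrase and needs no new data, visits or patients. The cost is one extra summary that is clinically less direct to read than the proportion obese.

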#### **Procedures and measures**

Practice staff will identify patients who meet the inclusion/exclusion criteria from their primary care practice electronic record. All eligible regular and normal attending patients will be invited to have a baseline interview (see below). Practice staff will send eligible patients a study pack containing an invitation letter (on practice letterhead) inviting them to take part in the study, an information sheet, describing the study, a ‘consent to contact’ form and a stamp addressed envelope. If patients are interested in finding out more about the study and speaking to a researcher, they will be asked to return the ‘consent to contact form’ to the study researcher in the stamped addressed envelope provided. The consent form will also ask the patient’s permission for the researcher to access their anonymised medical records even if they do not wish to be interviewed. A researcher will then telephone the patient to discuss the study further, answer any queries they may have, and if verbal consent is given, arrange a time for interview. One reminder letter (on practice letterhead) will be posted by practice staff to eligible participants who did not respond to the initial invite. In some instances where the GP feels the patient may be suitable for the study but the patient has not responded to invitations to take part, the GP may approach the patient directly and make an appointment to see them to explain the study.

Each patient will be interviewed to explore the presence or absence of psychiatric disorder including depressive disorder, anxiety disorder and somatoform disorder [52] using a structured psychiatric interview (SCID-1) [53], the presence and degree of severity of health anxiety over the last week on the Health Anxiety Inventory (HAI) [24], quality of life on the EQ5D [54], and information on health and social care, work and benefits using the Client Receipt Service Inventory (CSRI) [55] (Table 1).

**Table 1 T1:** Baseline interview

SCID	SCID-1 for DSM-IV (Structured Clinical Interview for Diagnostic and Statistical Manual of Mental Disorders)(First et al., 1997)
CSRI	CSRI Client Services Receipt Inventory (Beecham and Knapp 2001)
EQ5D	EQ5D Standardised instrument for use as a health measurement (Euroqol group 1990)
HAI Short Week	Health Anxiety Inventory (HAI, a 14 item self-rated measure of health anxiety, Salkovskis et.al, 2002) with a score above 21 indicating severe health anxiety.

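### Controls are matched on age, gender and practice, but the named between-group tests ignore the matching, and the one pair-conditional analysis is run within each group, where it cannot condition on pairs

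*Protocol article*

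**What the plan says.** *Recruitment* (case control study) says that regular attenders will be "matched by age, gender and practice to a normal attender to control for practice and socio-demographic characteristics", and that this is done "by practice staff who will write to the patients to request their participation in the study". The target is: "Approximately 100 regular attenders and 100 normal attenders will be recruited". On uptake it says: "Pilot work shows that 30-40% of regular attenders will agree to be interviewed but a higher proportion of normal attenders will agree".

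Hypothesis 2, under *Hypotheses*, names controls matched on the same three factors as the comparator for mental disorder, health anxiety, physical problems and trauma history.

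*Statistical analysis in case control study* gives 90% power for 100 against 100 at 48% versus 25%, two-sided 5%. It then names the univariate tests of difference between the groups: a t-test on means or geometric means, and "Chi-squared test will be used for group differences in categorical variables". Pairing is not mentioned. The last paragraph of that section plans regression "conditional on case–control matched pairs", with frequency of primary care contacts as the outcome, for regular and normal attenders separately.

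*Procedures and measures* describes the invitation differently: "All eligible regular and normal attending patients will be invited to have a baseline interview".

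**The concern.** The matching is there to control for practice and socio-demographic differences, and the hypothesis relies on it, but the tests that would answer the hypothesis treat the two groups as independent samples. The tests are named, so this is more than detail left to a later analysis plan. Three things are at stake.

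- **Precision.** If partners resemble each other on an outcome, an unpaired standard error is larger than it should be, so intervals are too wide and tests too cautious.
- **Control of confounding.** If pairs break because one member declines, the matching no longer guarantees balance on age, gender and practice, and a plain t-test or chi-squared test does not restore it.
- **Coherence.** The only analysis said to use the pairs does not compare the groups.

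**Working it through.** **Inputs.** From the protocol: 48% and 25%, 100 per group, two-sided 5%, 90% power, 30-40% consent among regular attenders. Not in the protocol, so assumed and shown as ranges: the within-pair correlation ρ (0 to 0.3) and consent among normal attenders, which is said only to be higher (40-70% used for illustration).

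**1. The plan's own power figure.** For two independent groups, the difference is d = 0.48 − 0.25 = 0.23 and the mean proportion is 0.365.
- SE under the null = √(2 × 0.365 × 0.635 / 100) = 0.0681.
- SE under the alternative = √((0.48 × 0.52 + 0.25 × 0.75) / 100) = 0.0661.
- Uncorrected: z = (0.23 − 1.96 × 0.0681) / 0.0661 = 1.46, so power is 92.8%.
- Continuity-corrected (subtract 1/100 from d): z = 1.31, so power is 90.5%; 99 per group are needed for 90%.

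The stated 90% therefore reproduces as an unmatched calculation.

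**2. Intact pairs, unpaired test.** With equal variances, the paired variance of a mean difference is (1 − ρ) times the unpaired one. The unpaired SE is thus too large by 1/√(1 − ρ) − 1, and the true size of a nominal 5% test is 2 × [1 − Φ(1.96/√(1 − ρ))]. For the 48% versus 25% contrast, the paired SE is √((0.2496 + 0.1875 − 2ρ × 0.2163) / 100), where 0.2163 = √(0.2496 × 0.1875).

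| Assumed ρ | Unpaired SE too large by | True size at nominal 5% | Paired SE (unpaired 0.0661) | Simulated power of planned chi-squared, 100 pairs |
|---|---|---|---|---|
| 0 | 0% | 5.0% | 0.0661 | 92.8% |
| 0.1 | 5.4% | 3.9% | 0.0628 | 93.6% |
| 0.2 | 11.8% | 2.8% | 0.0592 | 95.1% |
| 0.3 | 19.5% | 1.9% | 0.0554 | 96.1% |

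The simulated powers are for the uncorrected test, 20,000 runs each. Size falls and power does not.

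**3. Pairs formed before consent.** A pair survives only if both members agree, so the share intact cannot exceed the regular attenders' consent rate of 30-40%; at least 60-70% of invited pairs break. To recruit 100 regular attenders, 100/0.40 = 250 to 100/0.30 = 333 pairs must be invited. With independent control consent of 40-70% (assumed), 0.30 × 0.40 = 12% to 0.40 × 0.70 = 28% of invited pairs stay intact, and 40 to 70 of the 100 recruited regular attenders keep their own control.

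**4. The pair-conditional regression.** Each pair has one member in each group. Restrict the data to one group and every pair contributes a single person, so there is no within-pair contrast left to condition on. The two halves of that sentence cannot both hold.

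**The case against.** The case on the other side is substantial, and most of it stands as a limit on the point.

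- **Power.** A reader might infer that the 90% is not delivered because only complete pairs count. A McNemar test on 40-70 surviving pairs alone would have 55-80% power at ρ = 0, against 92% with 100 intact pairs. But the protocol does not plan that test. The planned t-test and chi-squared test drop nobody for a missing partner, and their power holds or rises over the assumed range.
- **Direction.** A reader might fear false positives. With non-negative within-pair correlation the size is at or below 5%. At ρ = 0 there is no error at all, and the protocol gives no correlation for any outcome.
- **Odds ratios.** Ignoring matching can attenuate an odds ratio, but these tests compare proportions and means. No unmatched odds ratio is planned; the one in that section belongs to the cited study.
- **No pairs at all.** Inviting every eligible patient might seem to rule out pairing. It does not: consenters can be matched afterwards, or the eligible patients may be those already selected. Replacing a control who declines is also detail that an article may leave to the full protocol.
- **Tension between the two parts.** The more pairs break, the smaller the standard-error problem. The two consequences are alternatives and do not add up at full size.
- **Wording.** The text says only t-test, so a paired version is conceivable. Unpaired is the natural reading, and an ordinary chi-squared test is unmatched by nature.

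This does not remove the mismatch between the matched hypothesis and the tests named for it, or the contradiction in the regression sentence.

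**Conclusion.** The point holds in a limited form. Hypothesis 2 is a matched comparison, and no analysis described for it uses the matching. With intact, positively correlated pairs, the cost is efficiency: standard errors about 5% to 20% too large for ρ of 0.1 to 0.3, none at ρ = 0, always in the conservative direction. The stated power is safe under the planned tests.

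If matching precedes consent, as the order in *Recruitment* implies, at most 30-40% of invited pairs can survive. Without re-matching, balance on age, gender and practice is then not assured, and the named tests adjust for none of them. The size and direction of any resulting bias cannot be worked out from the protocol. The correlations and the normal attenders' consent rate are assumptions; the 30-40% ceiling rests on the protocol's own uptake figure.

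**What to change.** 1. In *Statistical analysis in case control study*, make every group comparison matching-aware while keeping all participants: conditional logistic regression for binary outcomes and linear or count models for the rest, stratified by practice × gender × age band. Regression adjusted for age, gender and practice is an acceptable alternative. Five practices and two genders give 10 cells before age is split. A stratum holding only one group adds nothing to a conditional analysis, so age bands should be wide.
2. Use McNemar or paired tests only if controls are selected after the regular attender has consented.
3. Reword the regression sentence so that conditioning applies to the between-group model, and describe any within-group model of contact frequency without it.
4. Reconcile *Recruitment* with *Procedures and measures*: who is invited, when matching is done, and what happens when one member of a pair declines.

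The cost is analysis wording and, if controls are chosen after consent, a change in mailing order. The sample size is unchanged. The small downside is that age matching becomes banded, or a few model terms are added.

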#### **Hypotheses**

1. Most patients with regular attendance in primary care show chronic patterns of health care use with a duration of three or more years.

2. Compared to age, gender and practice matched normal attender controls, regular attenders are more likely to have depressive and anxiety disorders, somatoform disorders, high health anxiety, two or more active physical health problems, and a history of trauma or abuse in childhood or adulthood.

3. Compared to normal attender controls, regular attenders will incur up to five times the health care costs over the preceding 10 years but have a lower quality of life on the EQ5D.

4. Cognitive behaviour formulation and joint treatment between a cognitive behaviour therapist and a GP are feasible, acceptable and have clinical utility for regular attendance.

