### **Case control study of regular attenders and normal attenders**

#### **Inclusion criteria**

1. Regular attenders

· 30 or more face to face contacts with GP within the last 2 years established from the practice electronic record.

· Aged 18 years old and over.

· Consents to take part in the study

2. Normal attenders

· Between six and 22 face to face contacts with GPs over two years, established from the practice electronic record. A previous study of 828 consecutive attenders from eight Nottinghamshire practices revealed a median attendance of eight face to face consultations with GPs with approximately two thirds of the sample consulting between three and eleven consultations. Therefore we selected a normal consulting control group from patients who attended face to face appointments with the GP between six and 22 occasions.

· Aged over 18 years or older

· Consents to take part in the study

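### Regressions conditional on matched pairs but fitted to each attender group separately cannot estimate any covariate effect, and the within-group screen is a poor guide to what distinguishes the groups

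*Protocol article*

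**What the plan says.** Under Recruitment, each regular attender is "matched by age, gender and practice to a normal attender to control for practice and socio-demographic characteristics", with about 100 recruited to each group. A pair therefore contains one member of each group.

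The section on statistical analysis in the case control study first sets out univariate comparisons of the two groups (t-tests and chi-squared tests). It then states: "Multivariate regression analyses conditional on case–control matched pairs will be conducted". The purpose given for these regressions is "to identify factors significantly associated with frequency of primary care contacts by regular and normal attenders separately".

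The results feed a second step: "Important variables (either statistically significant or clinically important) for each group of patients will be used in a discriminant analysis". That step is meant to find the variables that "best reflect different characteristics of the two groups and separate them in principle of a maximum distance".

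The hypothesis served is a between-group one: "Compared to age, gender and practice matched normal attender controls, regular attenders are more likely to have depressive and anxiety disorders", followed by further conditions. The section lists logistic regression among its model types, but nowhere names group membership as a dependent variable.

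**The concern.** Two instructions in one sentence exclude each other. Conditioning on a pair uses only contrasts between its members. Fitting the groups separately removes one member from every pair, so no contrast is left.

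The obvious repair, dropping the conditioning, makes the models run but changes what they answer. They then describe what goes with more or fewer contacts among people already chosen for their GP attendance; entry as a regular attender requires "30 or more face to face contacts with GP within the last 2 years established from the practice electronic record". The discriminant analysis asks a different question: what distinguishes one group from the other. A variable can matter for one question and not the other.

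At stake is the multivariable part of secondary objective 2 and hypothesis 2. It is also the only described analysis that uses the matching, since the univariate tests mention no pairing.

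**Working it through.** **1. The plan's own figure.** Inputs from the statistical analysis section: 48% versus 25%, n = 100 per group, two-sided 5%, stated power 90%. With p̄ = (0.48 + 0.25)/2 = 0.365 and a continuity correction of 1/n:

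- null SE = √(2 × 0.365 × 0.635 / 100) = 0.0681
- alternative SE = √((0.48 × 0.52 + 0.25 × 0.75)/100) = 0.0661
- power = Φ[(0.23 − 0.01 − 1.96 × 0.0681)/0.0661] = Φ(1.31) = 90.5%

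The stated 90% reproduces (99 per group needed). Without the correction, power is 92.8% and 90 per group are needed. This is an unpaired two-group calculation and does not depend on the regression plan.

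**2. Can the regression be fitted as written?** For a linear model, conditioning on pair i replaces each covariate by its deviation from the pair mean, x − x̄ᵢ. With one member per pair this is 0 for everyone. For a conditional logistic or Poisson likelihood, a stratum contributes a term of the form exp(xβ)/Σexp(xβ). With one member it equals 1 whatever β is. Rank check, using 100 pair effects plus three covariates:

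| Data | Rows | Rank, pair effects only | Rank with 3 covariates |
|---|---|---|---|
| One group alone | 100 | 100 | 100 |
| Both groups | 200 | 100 | 103 |

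In one group the covariates add nothing to the rank, so none of their effects is estimable. In both groups together all three are. No effect size or distribution is assumed.

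**3. Does the significance screen find discriminators if the conditioning is dropped?** Illustration with 100 per group, 2,000 runs, a standard normal frequency score, linear regression on both factors in each group, and a factor picked if p < 0.05 in either group. The 48% and 25% come from the protocol; everything else is assumed.

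| Factor | Prevalence, regular vs normal | Within-group link to frequency | Picked |
|---|---|---|---|
| A, separates the groups | 48% vs 25% | none | 9.6% |
| B, does not separate | 30% vs 30% | 0.6 SD | 94.5% |

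The chance level for two tests is 1 − 0.95² = 9.75%, so the screen does not see factor A at all.

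**4. A less extreme case.** Here one factor drives both between-group and within-group differences. Assumptions: gamma-Poisson two-year counts with shape 1.2, factor prevalence 25%, groups selected at 30 or more and at 6 to 22, 100 per group, and the outcome is the selection count itself. Ranges reflect how the mean is set.

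| Assumed mean; rate ratio | Between-group power | Picked, regular | Picked, normal | Picked in either |
|---|---|---|---|---|
| 9; exp(0.4) | 95–98% | 47% | 12–14% | about 55% |
| 9; exp(0.5) | 99.6–99.7% | 63–65% | 16–19% | 68–70% |
| 16; exp(0.4) | about 79% | – | – | about 54% |

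The documents give no mean. The value 16 is twice the median of eight given under Inclusion criteria, just as 6 to 22 is twice three to eleven. The screen picks the factor less often than a direct comparison detects it in every row, but the gap narrows from about 40 to about 25 percentage points as the assumed mean rises.

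**The case against.** - **Another reading of the sentence.** Separate analysis could mean group-specific slopes in one pair-conditional model. That is estimable: 100 pair effects + 1 group term + 2 × 3 slopes = 107 parameters, and the rank on 200 rows is 107. Conditioning could also loosely mean adjusting for the matching factors. The first reading strains the wording, and both still model frequency rather than group membership. What stands is that a reworded model can be fitted.
- **The rest of the plan.** A reader might infer that the multivariable plan as a whole cannot be run, or that hypothesis 2 goes untested. The documents do not support this. The discriminant analysis is itself a joint multivariable analysis and can be fitted. The univariate comparisons address most of hypothesis 2 directly, and the sample size rests on such a contrast. This stands in full.
- **The screen.** A reader might infer that true discriminators are simply discarded. Variables may also enter as clinically important, the hypothesis 2 factors are obvious candidates for that route, and the discriminant step may select further. This softens the problem; it does not remove it for variables that depend on significance.
- **Truncation.** A reader might infer that the regression outcome is cut at 30, or at 6 and 22. Selection is on face-to-face GP contacts over two years without routine checks. The regression outcome is frequency of primary care contacts, with no period given, and the plan also collects telephone, home and nurse contacts over ten years. The outcome is related to the selection count but is not shown to be cut at those limits. Nor does the text say that counts will be analysed linearly.
- **Within-group questions are legitimate.** Correlates of frequency fit the stated interest in patterns of consultation. This stands, so those models need not be deleted.

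**Conclusion.** The point holds in two parts of unequal strength.

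The first is structural: as written, conditioning on 1:1 case-control pairs and fitting each group separately are incompatible, and no covariate effect is estimable. This needs no assumption beyond one member of each group per pair.

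The second is a mismatch of question. Screening on within-group association with frequency can miss variables that distinguish the groups and admit ones that do not. The direction is clear, but the size is not: the simulated rates depend on assumed means, effects and outcome definition, and they ignore the clinical-importance route.

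Data collection, recruitment, the univariate comparisons and the 90% power figure are untouched. This is a should-fix matter confined to one paragraph of secondary analysis.

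**What to change.** Reword the paragraph in three places:

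1. For the between-group question, fit one conditional logistic regression to both groups, with regular-attender status as the outcome, strata defined by matched set, and the hypothesis 2 factors as covariates.
2. Take the variables for the discriminant analysis from that model.
3. If within-group correlates of frequency are still wanted, label those models exploratory and drop the pair conditioning. Adjust for age, gender and practice, state the outcome and its period, and use a count model suited to it. Use a truncated model only if the outcome is the same GP count used for selection.

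The cost is wording only: no further data, patients or procedures.
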